#### 2.10.3. Statistical Analysis

For demographic variables of the intervention and control groups at baseline, descriptive statistics will be presented using mean and standard deviation for variables that are normally distributed and median and interquartile range for skewed continuous variables and proportion for categorical variables. Table 3 provides an overview of all primary and secondary outcome measures, their definitions and the methods to be used for evaluating the respective hypotheses.

For the continuous primary outcome of MVPA as well as continuous secondary outcomes based on health behavior, mental health and physical health measures at the six-month follow-up, the mean difference between the intervention and the control groups will first be evaluated using t-tests. Further adjustment for respective baseline values of the outcome variables (where available) of the individual will be made via multiple linear regression analysis. For accelerometer related outcomes where no baseline value is available, adjustment for total self-reported MVPA of the individual will be made via multiple linear regression analysis. For categorical outcomes at 6-months (e.g., depression/anxiety levels from K10) logistic regression will be conducted adjusting for the same covariates.

Subgroup analysis based on the report of engagement in physical activity in parks will be performed to investigate the effect of the intervention on the primary and secondary outcomes.

Up-to-date versions of R (Auckland, New Zealand) and STATA (Texas, TX, USA) will be used to conduct the analysis. All evaluations will be made based on intention to treat, assuming a two-sided test at the 5% level of significance. Effect sizes and 95% confidence intervals will also be reported for the respective outcome measures.

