**Secondary outcome**					
Physical activity	Total physical activity volume ^a^	Accelerometer			X
Light and sedentary activity	Time spent in light and sedentary activity	Accelerometer			X
Physical activity	Frequency, intensity, time and type	Self-administered questionnaire—GPAQ	X	X	X
Sedentary activity	Time spent sitting	Self-administered questionnaire—IPAQ	X	X	X
Park usage	Time spent in parks last month, physical activity time in parks on a typical month.	Self-administered questionnaire	X	X	X
Mental wellbeing	Wellness	Self-administered questionnaire—SF-12, K10, WHO5, WHOQoL-BREF ^b^	X		X
Anthropometry	BMI **^c^**—weight in kilograms divided by height in meters squared	BMI machine	X		X
Biochemistry	Blood lipids, fasting blood glucose	Blood samples	X		X
Blood pressure	Systolic and diastolic	Dinamap blood pressure monitor	X		X

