**Process indicator ^d^**					
Motivation to exercise	Social support for physical activity, reasons to engage, physical activity knowledge	Self-administered questionnaire—BREQ-2		X	
Attitudes and behaviors	Perceived changes in participants’ attitudes and behaviors towards physical activity and park use, intention to continue group exercise	Self-administered questionnaire.			X
Satisfaction with and quality of program	Satisfaction with and quality of prescription sheet and parks brochure	Self-administered questionnaire		X	
	Satisfaction with and quality of physical activity planning sheet	Self-administered questionnaire		X	
	Satisfaction with and quality of phone counselling	Self-administered questionnaire			X
	Satisfaction with and quality of program overall	Self-administered questionnaire			X

V0 = Baseline, V1 = 3-month mid-intervention follow-up, V2 = 6-month follow-up at completion of the intervention. GPAQ Global Physical Activity Questionnaire (sections on work, transportation and recreational activities); IPAQ International Physical Activity Questionnaire, Part 5: Time Spent Sitting, item 26 and 27; SF-12, 12 item short-form survey, item 1; K10 Kessler Psychological Distress Scale; WHO5 WHO (Five) Well-being Index; WHOQoL-BREF WHO Quality of Life Short Form; BREQ-2 Exercise Regulation Questionnaire. ^a^ We use Euclidean Norm Minus One (ENMO) as the ‘total volume’ measure. It reflects ‘average acceleration’ in gravitational units (mg). [28,29]. ^b^ WHOQoL-BREF administered only at 6-month follow-up. **^c^ Body Mass Index (BMI). ^d^** Process indicators only administered to intervention group.

**Table 3 ijerph-15-01154-t003:** Outcome measures, their definitions and methods for evaluating the hypotheses.

Outcome	Hypothesis	Definition	Analysis
(1) Primary			
Time spent on MVPA ^a^—objective measure	Improvement in MVPA in intervention group as compared to control group at six months	Time spent on MVPA in minutes per week as measured by the accelerometer	*t*-test. Linear regression
(2) Secondary			
a. Health behaviors	Improvement in health behaviors in intervention group as compared to control group at six months		
Total volume of physical activity		Total activity volume as measured by the accelerometer ^b^	*t*-test. Linear regression
Time spent on light and sedentary activity		Time spent per week on light and sedentary physical activity as measured by the accelerometer	*t*-test. Linear regression

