Time spent on MVPA—subjective measure		Self-reported time (minutes) per week spent on MVPA as recorded in questionnaire	*t*-test. Linear regression
Time spent in parks; time spent being physically active in parks		Self-reported time (minutes) in parks in the past month; and time spent engaging in physical activity in parks in a typical month as recorded in the questionnaire	*t*-test. Linear regression
Recreational MVPA time		Self-reported time (minutes) per week spent on recreational activity as measured by GPAQ^a^	*t*-test. Linear regression
Sitting time		Self-reported time (minutes) per week spent sitting as measured by IPAQ ^a^	*t*-test. Linear regression
b. Mental wellbeing	Improvement in mental wellbeing in intervention group as compared to control group at six months		
Mental wellbeing		Self-reported mental wellbeing as measured by SF-12 (1-item, general health), K-10, WHO5 and WHOQOL-BREF^a^	*t*-test. Linear regression. Logistic regression
c. Physical health	Improvement in physical health in intervention group as compared to control group at six months		
Body Mass Index (BMI)		Weight in kg divided by height squared in m measured by BMI machine.	*t*-test. Linear regression
Fasting blood glucose		Fasting blood glucose in mmol/L. Laboratory assessment	*t*-test. Linear regression
Systolic and diastolic blood pressure		Systolic and diastolic blood pressure in mmHG measured by a Dinamap blood pressure monitor	*t*-test. Linear regression

^a^ Abbreviations: MVPA, moderate-to-vigorous physical activity; GPAQ, Global Physical Activity Questionnaire; IPAQ, International Physical Activity Questionnaire. SF-12, 12 item short-form survey; K10, Kessler Psychological Distress Scale; WHO5, WHO (Five) Well-being Index; WHOQoL-BREF, WHO Quality of Life Short Form; BREQ-2, Exercise Regulation Questionnaire.^b^ We use Euclidean Norm Minus One (ENMO) as the ‘total volume’ measure. It reflects ‘average acceleration’ in gravitational units (mg) [28,29].

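### The primary outcome and every continuous secondary outcome get both an unadjusted t-test and a regression at 5%, with neither named as deciding and the primary's covariate left undated

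*Protocol article*

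**What the plan says.** Section 2.10.3 sets out two steps for the primary outcome and the continuous secondary outcomes at six months. In the first step, "the mean difference between the intervention and the control groups will first be evaluated using t-tests". The second step is regression: "Further adjustment for respective baseline values of the outcome variables (where available) of the individual will be made via multiple linear regression analysis".

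The accelerometer is worn only at V2 (Table 2), so the primary outcome and the other accelerometer outcomes have no baseline value. For these, "adjustment for total self-reported MVPA of the individual will be made via multiple linear regression analysis". That sentence names no visit.

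For categorical outcomes, "logistic regression will be conducted adjusting for the same covariates"; no t-test is planned.

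The section introduces Table 3 as giving the outcomes, their definitions and "the methods to be used for evaluating the respective hypotheses". The primary row of Table 3, defined as "Time spent on MVPA in minutes per week as measured by the accelerometer", lists a t-test and linear regression side by side. The secondary rows do the same, and mental wellbeing adds logistic regression. All evaluations are two-sided at 5%.

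Table 2 shows the activity questionnaire (GPAQ; "Frequency, intensity, time and type") at V0, V1 and V2. Self-reported MVPA is also a secondary outcome in Table 3 ("Self-reported time (minutes) per week spent on MVPA as recorded in questionnaire").

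**The concern.** Two tests are attached to one primary hypothesis, each at the full 5%, and the article does not say which one answers it. If they disagree, the conclusion depends on a choice made after the results are known, in a trial whose participants and staff knew the allocation. If either may count, the 5% level is exceeded. If the t-test counts because it comes first, the trial sets aside V0 information that it already holds.

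A second gap concerns the covariate in the primary regression. Its label would also fit the three- or six-month questionnaire. Those values arise after randomisation and can be moved by the intervention, so adjusting for one of them would take out part of the effect being estimated.

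**Working it through.** **Inputs from the article.** Difference 30 min/week, SD 60, alpha 0.05, power 80%, 64 per group, 20% drop-out, 80 per group (section 2.6); 1:1 allocation (section 2.1); two-sided test (section 2.10.3). The article gives no correlation r between covariate and outcome, so r is assumed over a range.

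**Stated sample size.** The normal approximation is n = 2 × (1.96 + 0.842)² × (60/30)² = 62.8, so 63 per group. The exact t-test calculation gives 63.77, so 64, with 80.1% power at 64. Then 64 / 0.80 = 80 per group. The stated figures reproduce as an unadjusted t-test.

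**Error rate if either test may carry the claim.** Under the null, the unadjusted and adjusted statistics correlate at √(1 − r²): 0.954 at r = 0.3 and 0.866 at r = 0.5. The bivariate-normal probability that at least one exceeds 1.96 in absolute value is 6.4% and 7.3%. A simulation (100,000 trials per scenario, 64 per arm, baseline covariate) agrees. It also shows how often the two tests disagree under the planned 30-minute effect:

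| Assumed r | Type I error, either test | Tests disagree under the planned effect |
|---|---|---|
| 0.1 | 5.6% | not run |
| 0.2 | 5.9% | 4.6% |
| 0.3 | 6.3% | 6.9% |
| 0.5 | 7.4% | 12.6% |

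**Precision.** The unadjusted standard error divided by the adjusted one is 1/√(1 − r²). At an assumed r = 0.7 this is 1/√0.51 = 1.40.

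For the primary outcome, the residual SD after adjustment is 60√(1 − r²), and approximate power at 64 per group is Φ(30 / [60√(1 − r²) × √(2/64)] − 1.96):

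- r = 0: 81% (80.1% by the exact t-test)
- r = 0.2: 82%
- r = 0.3: 84%
- r = 0.5: 90%

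The planned size is therefore enough whichever test is named.

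**Undated covariate.** Suppose the V2 self-report were used and the intervention raised it by 0.5 SD (an assumption). The adjusted estimate becomes 30 − r × 0.5 × 60 min/week:

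| Assumed r (within group) | Adjusted estimate | Simulated power of the regression |
|---|---|---|
| 0.2 | 24 min/week | 60% |
| 0.3 | 21 min/week | 51% |
| 0.5 | 15 min/week | 34% |

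The t-test stays at 80% throughout. With a V0 covariate, the simulated adjusted estimate stays at 30.

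**The case against.** The best defence is that the article does imply an order. The t-test comes first, the regression is described as a further step, and the sample size reproduces as a t-test. A reader could fairly conclude that the t-test leads and the regression supports it. This stands as an inference, but it is not a designation: order of presentation does not settle which result decides, and Table 3 gives both methods as evaluating the same hypothesis. Nor is this a detail left to an analysis plan, because the article itself fixes two methods and does not choose.

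Four stronger readings are tempting, and the article does not support them:

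- **The primary is adjusted for a post-randomisation value.** The covariate is offered as a substitute where an outcome has no baseline value, directly after a sentence about baseline values. V0 is the natural reading. If V0 is meant, it does no harm that self-reported MVPA is also a six-month outcome; that is ordinary covariance adjustment. The fall from 30 to 24, 21 or 15 minutes shows why the label matters. It does not describe what the plan prescribes.
- **The trial's type I error is 6% to 7%.** That needs a rule that either test suffices, which the article nowhere states.
- **Every outcome is tested twice, or precision is lost on BMI, glucose and blood pressure.** Categorical outcomes get logistic regression only. Baseline-adjusted regression is already planned for those physical measures, so precision is lost only if the t-test decides.
- **Leaving out age, sex, BMI or sitting time is an error.** A randomised comparison does not require them, and the article gives no figure showing that they predict the outcome strongly.

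The correlations may also be low. Entry was limited to people reporting under 150 minutes of weekly exercise, which may narrow the covariate's range. At r of 0.1 to 0.2 the inflation is below one percentage point.

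**Conclusion.** The point holds for the primary outcome and the continuous secondary outcomes: two tests at 5%, neither designated. The consequence is moderate. It is an either-test error of 6.3% to 7.4% at assumed correlations of 0.3 to 0.5, or a standard error about 1.4 times larger at an assumed 0.7 if the t-test is the one relied on. The missing visit label on the primary covariate is a gap in wording with a probable intended meaning, but the cost of a wrong reading is large enough to close it. The size of each effect rests on assumed correlations, and the covariate example also on an assumed 0.5 SD shift in self-report. The absence of a named deciding test rests on the text alone.

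**What to change.** Change section 2.10.3 and Table 3 as follows, before outcome data are examined by arm; the analysis is still described in the future tense.

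- **Deciding analysis.** Name the baseline-adjusted linear regression, two-sided at 5%, as the single analysis that answers each continuous hypothesis. Label the t-test supportive.
- **Primary and other accelerometer outcomes.** Adjust for V0 (baseline) GPAQ total self-reported MVPA, with the visit written in the text.
- **Continuous secondaries with a V0 value.** Adjust for that value.
- **WHOQoL-BREF.** A footnote to Table 2 lists it at six months only, so neither existing rule supplies a covariate. Use an available V0 wellbeing score such as WHO5.
- **Categorical outcomes.** Keep the logistic regression.

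Further V0 covariates (age, sex, BMI, sitting time) are optional; if used, list them in advance. The cost is a few words and one or two degrees of freedom. No new data are needed, and the sample size does not change.

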#### 2.5.2. Secondary Outcomes

Secondary outcome measures are defined as the differences between the mean values in the intervention and the control groups at six months follow-up in health behaviors, mental wellbeing and physical health.

Measures for health behaviors related to physical activity include the total volume of activity reflecting average acceleration in gravitational units (mg), time spent in light intensity physical activity and sedentary activity measured by accelerometer, as well as recreational activity time per week, subjectively-measured total MVPA time per week and sedentary time per week assessed by self-administered questionnaire. The physical activity questions come from the previously validated WHO Global Physical Activity Questionnaire [22]. The questions on sedentary time come from the validated International Physical Activity Questionnaire [23]. Self-reported time spent in parks in the past month and time spent doing physical activity in parks in the past month were also included in the self-administered questionnaire at baseline, three months and six months follow-up.

The secondary outcome measures for mental wellbeing include the difference in self-reported quality of life and mental wellbeing between the intervention group and the control group at six months follow-up. This was measured by previously validated survey questions including the general health item from the SF-12, K-10, WHO5 and the WHOQOL-BREF [24,25,26,27]. The physical health measures are objectively-measured Body Mass Index (BMI), fasting blood glucose levels as well as systolic and diastolic blood pressure, as assessed prior to baseline and during the health screening visit at six months follow-up.

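### Accelerometer sedentary time is adjusted only for self-reported MVPA, although baseline sitting time, a closer proxy, is scheduled in both arms; the adjusted comparison is valid but may be less precise than it could be

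*Protocol article*

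**What the plan says.** Section 2.10.3 compares the arms first by t-test. It then adjusts by linear regression for each outcome's own baseline value where one exists. For the remaining device outcomes it sets a single rule: "For accelerometer related outcomes where no baseline value is available, adjustment for total self-reported MVPA of the individual will be made via multiple linear regression". It makes no exception for sedentary time.

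The rule applies to sedentary time because Table 2 lists "Time spent in light and sedentary activity" by accelerometer at V2 only. Table 3 defines the outcome as "Time spent per week on light and sedentary physical activity as measured by the accelerometer" and assigns it a t-test and a linear regression. Section 1.1 names accelerometer-measured sedentary behaviour among the secondary objectives.

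Table 2 also schedules "Time spent sitting" ("Self-administered questionnaire—IPAQ") at V0, V1 and V2. Section 2.5.2 gives the source: "The questions on sedentary time come from the validated International Physical Activity Questionnaire". Section 2.1 has both arms assessed at baseline, and the only arm restriction in the Table 2 footnotes is on process indicators. Baseline sitting time is therefore planned for both arms.

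**The concern.** The plan's own logic is to adjust each outcome for its baseline value and, where the device gives none, for a self-reported stand-in. For the primary outcome the stand-in is self-report of the same behaviour. For sedentary time the plan holds a self-report of a closely related behaviour, sitting, but prescribes self-report of a different one, moderate-to-vigorous activity. Under the general rule, baseline sitting serves only the self-reported sitting outcome.

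What is at stake is efficiency in one secondary model. If baseline sitting predicts accelerometer sedentary time beyond what MVPA predicts, leaving it out leaves residual variance that could have been removed, and chance imbalance in baseline sitting goes unadjusted. The rule is stated explicitly, so this is not a detail left to a separate analysis plan.

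**Working it through.** **Inputs from the protocol article.** Section 2.6: difference 30 min/week, SD 60, alpha 0.05, power 80%, 20% drop-out. Section 2.10.3: two-sided testing. Section 2.1: 1:1 allocation. No SD, effect size or correlation is given for sedentary time.

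**The plan's own figure.** Normal approximation: n per arm = 2 × (1.960 + 0.842)² × (60/30)² = 2 × 7.849 × 4 = 62.8, so 63. The t-test version gives 63.8, so 64. With drop-out, 64/0.8 = 80 per arm and 160 in total. The stated sample size reproduces. It was derived for MVPA; here it serves only to give the number analysed, about 2 × 64 = 128.

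**Adding sitting time.** Let r be the partial correlation of baseline sitting with accelerometer sedentary time, given self-reported MVPA. Adding sitting to a model with arm and MVPA multiplies the residual variance by 1 − r² and the standard error of the arm difference by √(1 − r²), before the lost degree of freedom. The values of r are assumptions:

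| r (assumed) | Variance cut, r² | √(1 − r²) | Fall in standard error |
|---|---|---|---|
| 0.1 | 1% | 0.995 | 0.5% |
| 0.2 | 4% | 0.980 | 2.0% |
| 0.3 | 9% | 0.954 | 4.6% |
| 0.4 | 16% | 0.917 | 8.3% |
| 0.5 | 25% | 0.866 | 13.4% |

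**Break-even.** With 128 analysed, residual degrees of freedom go from 128 − 3 = 125 to 128 − 4 = 124. The estimated residual variance falls only if (1 − r²)/124 < 1/125, that is r² > 1/125 = 0.008, or r above about 0.09.

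**Partial versus simple correlation.** What counts is what sitting adds after MVPA. If MVPA correlates −0.2 with both sedentary time and sitting, and sitting correlates 0.3 with sedentary time, then r = (0.3 − 0.04)/(1 − 0.04) = 0.27. The variance cut is 7.3%, and √(1 − 0.073) = 0.963, a 3.7% fall in standard error.

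**Replacing MVPA with sitting.** The standard error ratio is √[(1 − r_sit²)/(1 − r_MVPA²)], using simple correlations with the outcome. With r_MVPA = −0.3 and r_sit = 0.1 it is √(0.99/0.91) = 1.043, which is worse. With r_MVPA = −0.1 and r_sit = 0.5 it is √(0.75/0.99) = 0.870, which is better. A swap can lose precision; an addition costs at most about one degree of freedom.

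**The case against.** The case for leaving the rule alone is fair. One prespecified covariate for all device outcomes is simple and legitimate, and nothing in the document contradicts it. The regression is also the second step: the unadjusted t-test comes first and no covariate affects it. IPAQ sitting is recalled sitting, whereas the device records movement at the non-dominant wrist, worn at all times for seven days about six months later (section 2.10.1). The two are related but not the same, so the partial correlation may be small. Completeness of the baseline sitting items is not reported either.

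All of this stands, and it limits the point to an optional gain. It does not remove it, because a closer baseline measure is already scheduled and costs almost nothing to use.

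A reader might go further in three ways that the documents do not support:

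- **That precision is definitely lost.** This needs a non-trivial partial correlation, and none is given.
- **That power for sedentary time falls short by a stated amount.** The only effect size and SD in the article belong to MVPA, so a power figure built on them does not describe this outcome.
- **That accelerometer light activity needs the same change.** Sharing the waking day with sitting is a weak argument, because MVPA shares that day too.

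**Conclusion.** The point holds as a minor matter of efficiency. Section 2.10.3 fixes self-reported MVPA as the only named covariate for accelerometer sedentary time, while a closer baseline proxy is scheduled in both arms and goes unused for that outcome. The possible gain is a fall in standard error of about 0.5% to 13% for assumed partial correlations of 0.1 to 0.5, and it is negligible below about 0.1. This assumes about 128 analysed and largely complete baseline sitting items; the documents settle neither the correlation nor the completeness.

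A reader might take the mismatched covariate as a source of bias. It is not: randomisation keeps the comparison valid under either covariate set, and the primary MVPA analysis is untouched.

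**What to change.** Add one sentence to section 2.10.3:

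> For accelerometer sedentary time, the regression will include baseline (V0) IPAQ sitting time in addition to baseline (V0) self-reported MVPA.

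Add sitting time; do not substitute it for MVPA. Leave the primary MVPA model and the light-activity model as they are. Naming V0 is useful because the current sentence does not say which visit's self-report is meant, and both questionnaires are also given at V1 and V2, after randomisation.

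The cost is one degree of freedom and a simple imputation of any missing baseline sitting values, so that no participant is dropped for a missing covariate. No new data are needed. Sections 2.10.2 and 2.10.3 describe questionnaire data entry and analysis in the future tense, so the sentence can be added if this is done before the outcome data are analysed.
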